### Side effects of aspirin

In the Cochrane Library review (12 studies, 22,309 patients), no maternal or foetal accidents were reported [32]. In particular, no increases in the frequency of retro-placental haematoma or maternal haemorrhage were observed. Some trials, however, reported an increased frequency of maternal bleeding. This was the case of the ERASME study, in which the frequency of minor bleeding was significantly (though moderately) higher (RR 1.25, 95% CI: 1.03-1.54) [24].

With respect to the foetus, no increased risk of bleeding, particularly intra-cranial bleeding, was highlighted in the meta-analyses of published trials. In light of the results of the exposure registers of numerous pregnancies to aspirin, including during embryogenesis, before 11 WA, there are no formal arguments in favour of an increased risk of malformation.

In our trial, maternal haemorrhagic events will be collected.

### Trials on primiparous women

Only one prospective randomised trial has tested, on 3,294 primiparous women, the efficacy of systematic prevention of pre-eclampsia by treatment with 100 mg aspirin. The incidence of pre-eclampsia was not reduced in the aspirin group (RR 1.08, 95% CI: 0.64-1.83). Similarly, no significant reduction in the frequency of arterial hypertension (all forms), of maternal pre-eclampsia complications, in the incidence of perinatal death or in birth weights lower than the 10th percentile was highlighted [23,40]. In this study, the prevalence of pre-eclampsia was only of 1.6% in the control group and patients were included between 14 and 20+6 WA (mean gestational age 16+3 WA).

In this same trial, a third randomisation arm (Doppler ultrasound at 22-24 WA and aspirin in the event of bilateral notching or mean resistance index greater than 0.61) was offered to a fraction of the patients due to the availability of uterine Doppler ultrasonography in only half of the investigation centres. By comparison with the placebo group, this study showed that such a strategy applied to primiparous women did not entail a significant reduction in the risk of pre-eclampsia (RR 1.55, 95% CI: 0.7-3.3), of hypotrophy ≤3rd percentile or of perinatal death [40].

### Subsequent research prospects

Despite more than 30 years of prospective randomised trials and the involvement of more than 30,000 patients in these trials, the controversy surrounding the efficacy of aspirin in the prevention of pre-eclampsia and IUGR persists [37]. In its recent report on "the effect of antiplatelet agents in preventing the onset of pre-eclampsia or its complications"; the Cochrane Collaboration concluded as follows: "Antiplatelet agents have moderate effects on the prevention of pre-eclampsia and its consequences. Further trials are required to assess which patients are most likely to benefit, when treatment is best started, and at what dose." [35].

Recent advances in the early screening of pre-eclampsia, using uterine artery Doppler ultrasonography during the first trimester, open a new line of research into the efficacy of aspirin in primary prevention. The theoretical benefits are two-fold:

- This is early screening and should thus enable the initiation of treatment at a gestational age when trophoblast invasion has not yet begun. It will thus have a greater chance of being more effective.
- It does not add the need for additional examinations relative to the usual follow-up of pregnancy, only an evaluation involving a simple examination (Doppler ultrasound of the uterine arteries) that falls within the expertise of most professionals performing obstetrical ultrasonography.

## Identifying the population at risk

Due to the good tolerance of low-dose aspirin and to the severity of the maternal and foetal consequences of pre-eclampsia, we considered it essential to choose a test selecting the patients to treat with high sensitivity, despite a poor specificity.

Moreover, to facilitate patient selection, we selected a number of easily identifiable Doppler criteria (notch for which the lowest PI ≥1.7).

We also deliberately opted to ignore screening strategies combining Doppler ultrasonography and medical history or Doppler ultrasonography and biochemical assays (PAPP-A, free β-hCG, endothelial growth factors). For the former, the reasons were, besides the complexity of some of the selected criteria, the fact that primiparous women, by definition, have no obstetrical history (that with the greatest weight) and that the other factors (obesity, chronic hypertension, diabetes, Afro-American ethnicity) pertain only to a small proportion of patients. As for the strategies based on a combination of Doppler ultrasound of the uterine arteries with biochemical marker assays, their evaluation is currently incomplete and their implementation on a large population is too expensive to allow their use in clinical practice [41-42].

In our starting hypothesis, we thus selected our study population considering that the presence of bilateral notching on the Doppler ultrasound of the uterine arteries and/or the lowest PI ≥1.7 during the first trimester, would allow us to detect 75% of pre-eclamptic patients or those with intrauterine growth retardation with a specificity of 65% [31].

# Summary of benefits, if any, and foreseeable and known risks to the persons involved in the research

The expected benefits of preventive treatment are a 20% reduction in the incidence of pre-eclampsia and hypotrophy (≤5th percentile). We also hope for a reduction in the frequency of severe pre-eclampsia and its maternal complications, premature births and perinatal deaths.

The risks are dominated by a slightly increased risk of minimal maternal bleeding (epistaxis, gingivorrhagia, vaginal bleeding, rectal bleeding, bruising). There are no reports in the literature of a significant increase in major maternal bleeding (RPH, postpartum haemorrhage, etc.) or of a significant increase in major or minor neonatal bleeding. Exposure of a large number of pregnancies to low-dose aspirin eliminates the risk of foetal malformations when used at ≤ 150 mg/day [35]. Moreover, initiation of treatment in our trial after the ultrasound of 11-14 WA limits exposure during embryogenesis.

Patients will be clearly informed that due to the antiplatelet effect and an increased risk of spinal haematoma in such cases, they may not be able to benefit from locoregional (epidural) anaesthesia if the discontinuation of treatment is ≤ 8 days at the time of use (especially in case of premature delivery).

# Effects

To answer to the hypothesis of the efficacy of aspirin prescribed early (before the onset of trophoblast invasion) and at the highest dose proposed (in order to overcome a lack of efficacy by dose effect) in a "high-risk" subgroup of patients of 1/3 of primiparous women encompassing 75% of patients who will develop placental insufficiency.

# Research objectives

## Primary objective

To test the efficacy of low-dose aspirin (160 mg/day), started at an early stage (≤ 15 WA completed), in primiparous patients selected as "at risk" on the presence of bilateral notch and/or high pulsatility index on the uterine arteries, in a pragmatic, double-blind, randomised trial to prevent the occurrence of pre-eclampsia during pregnancy or neonatal hypotrophy ≤ 5th percentile.

## Secondary objectives

- To evaluate the effect of aspirin separately on each of the primary endpoint parameters (pre-eclampsia on the one hand and neonatal hypotrophy on the other hand)
- To evaluate the efficacy of aspirin in preventing early onset and severe forms of pre-eclampsia (occurring before 32 WA)
- To evaluate the efficacy of aspirin in preventing the need for birth before 34 WA, perinatal death (death between the 22nd WA and postnatal day 7)
- To compare in each of the two groups (aspirin and placebo) the delivery route and the frequency of use of loco-regional analgesia.
- To specify the maternal tolerance of the treatment
- To evaluate compliance with the treatment

# Research endpoints

## Primary endpoint

Occurrence of pre-eclampsia during pregnancy or birth weight ≤ 5th percentile:

- Pre-eclampsia, defined as gravid arterial hypertension and proteinuria after 20 WA or in the postpartum period. Arterial hypertension is defined as a systolic blood pressure ≥ 140 mmHg and/or a diastolic pressure ≥ 90 mmHg, measured twice and separated by at least 4 hours. Proteinuria is positive if it is greater than 500 mg/L.
- A birth weight ≤ 5th percentile for the gestational age on AUDIPOG curves adapted to the sex of the newborn and the maternal body mass index (individual curves) [40].

### Secondary endpoints

The following endpoints will be analysed:

- Gestational age at onset of early pre-eclampsia (onset before 32 WA)
- Occurrence of severe pre-eclampsia defined by one of the following criteria:
  - Systolic blood pressure ≥ 160 mmHg and/or diastolic ≥ 110 mmHg
  - Proteinuria ≥ 5 g/day
  - Diuresis ≤ 400 mL/day or ≤ 20 mL/h
  - HELLP syndrome (thrombocytopenia ≤ 100,000 platelets/mm3, AST ≥ 70 IU/L, haemolysis with schizocytes and/or LDH 600 IU/L or haptoglobin < 0.4 g/L)
  - Eclampsia
  - Acute pulmonary oedema
  - RPH (Evocative clinical picture and/or histological confirmation by anatomopathological examination of the placenta)
  - IUFD
- Induced prematurity (triggering and/or maturation, caesarean section)
- Occurrence of perinatal death (death between the 22nd WA and postnatal day 7) not attributable to a cause other than placental insufficiency
- Delivery route: vaginal delivery or caesarean section. Elective caesarean sections (reason for planning) and emergency caesarean sections will be dissociated
- Use of loco-regional analgesia
- Tolerance will be studied from the elements collected from adverse event reports, but also from the "patient" records submitted at the time of inclusion
- Compliance will be evaluated by counting the treatments returned by patients

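### The early pre-eclampsia endpoint is onset age among affected women, which cannot show prevention; the preterm-birth and perinatal-death endpoints also depart from their objectives

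*Protocol*

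**What the plan says.** Section 6.2 of the Protocol states the objectives as prevention. One is "To evaluate the efficacy of aspirin in preventing early onset and severe forms of pre-eclampsia (occurring before 32 WA". Another is "preventing the need for birth before 34 WA, perinatal death (death between the 22nd WA and postnatal day 7", with no restriction by cause.

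Section 7.1.1 lists the endpoints. For early disease it gives "Gestational age at onset of early pre-eclampsia (onset before 32 WA". For severe disease it gives "Occurrence of severe pre-eclampsia defined by one of the following criteria". For preterm birth it gives "Induced prematurity (triggering and/or maturation, caesarean section", with no cut-off week. For death it gives "Occurrence of perinatal death (death between the 22nd WA and postnatal day 7) not attributable to a cause other than placental insufficiency". The Abstract carries the same objectives and the same endpoints, so the difference is not a slip in one place.

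Section 12.5 adds a secondary analysis that separates early and severe pre-eclampsia. It names neither a measure nor a test for it, and it mentions neither birth before 34 WA nor perinatal death.

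**The concern.** Onset age among early cases is defined only after the event that the objective seeks to prevent. The women compared are no longer the randomised groups but the subsets in which prevention failed. If aspirin prevents early disease, the women it helped contribute nothing. A between-arm difference in mean onset age therefore has no fixed relation to whether early disease was prevented: it can be zero, or point the wrong way, when the objective is met.

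The other two mismatches are simpler. Without the 34-week cut-off, the preterm-birth endpoint also counts indicated preterm deliveries after 34 WA, so the quantity named in the objective is not itself listed. The perinatal-death endpoint needs a judgement of cause, for which the protocol describes no process, and it covers only part of the stated objective.

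At stake is how three secondary results will be reported. Where the objectives name one quantity and the endpoint list another, the choice between them stays open after results are known.

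**Working it through.** **Step 1. Objectives against endpoints.**

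| Topic | Objective (6.2) | Endpoint (7.1.1) | Difference |
|---|---|---|---|
| Early pre-eclampsia | Prevent it before 32 WA | Onset age, given onset before 32 WA | Conditions on the event |
| Severe pre-eclampsia | Prevent it (before 32 WA) | Occurrence, no week limit | Occurrence is counted; the limit is missing |
| Preterm birth | Need for birth before 34 WA | Induced prematurity | 34 WA cut-off missing |
| Perinatal death | 22 WA to day 7, any cause | Same window, restricted by cause | Narrower |

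In the same list the protocol words severe pre-eclampsia and perinatal death as occurrences. Early pre-eclampsia is the one worded conditionally.

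**Step 2. The plan's own figure.** The protocol gives no number for these endpoints. Its primary sample size reproduces: 21.2% against 18.0%, two-sided 5%, 80% power, pooled variance and no continuity correction give 2415 per arm; 2415 × 1.024 = 2473; 2473 / 0.995 = 2485.4, rounded up to 2486. Nothing in this point bears on it; 2473 is used in step 5.

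**Step 3. What a true delay does to the listed measure.** Assumption, not in the protocol: among women with pre-eclampsia, onset is normal with mean μ = 36 WA and SD σ of 3 or 4, and aspirin delays every onset by two weeks, so μ becomes 38. With a = (32 − μ)/σ, the early share of cases is Φ(a) and the mean onset among early cases is μ − σ·φ(a)/Φ(a).

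- σ = 4, μ = 36: a = −1; share 15.9%; mean 36 − 4 × 0.2420/0.1587 = 29.9 WA.
- σ = 4, μ = 38: a = −1.5; share 6.7%; mean 38 − 4 × 0.1295/0.0668 = 30.2 WA. Early cases fall by 1 − 6.68/15.87 = 58%.
- σ = 3, μ = 36: a = −1.33; share 9.1%; mean 30.6 WA.
- σ = 3, μ = 38: a = −2; share 2.3%; mean 30.9 WA. Early cases fall by 1 − 2.28/9.12 = 75%.

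Mean onset among early cases moves by about 0.3 weeks in both settings.

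**Step 4. Other mechanisms.** A simulation took the 12.7% pre-eclampsia rate from section 12.1 and an assumed onset of N(36, SD 3.5).

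| Scenario | Early pre-eclampsia, all women | Mean onset, early cases |
|---|---|---|
| Control | 1.61% | 30.26 WA |
| Half of all cases prevented at random | 0.80% | 30.26 WA |
| 60% of cases at 28–32 WA prevented | 0.73% | 29.86 WA |
| Every onset delayed two weeks | 0.55% | 30.58 WA |

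In the second row the risk halves and the listed measure does not move. In the third the risk falls by more than half and onset among the remaining cases is earlier, which would look like harm.

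**Step 5. How many women contribute.** Over an assumed early rate of 0.5% to 2%, the control arm yields 2473 × 0.005 ≈ 12 to 2473 × 0.02 ≈ 49 onset ages.

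**The case against.** The strongest reply is section 12.5. It treats early and severe pre-eclampsia as components of the primary endpoint, which is itself an occurrence, and it compares the two main components by occurrence. The natural reading is that early pre-eclampsia will be compared in the same way, which is the remedy asked for here. Severe pre-eclampsia is already an occurrence endpoint. Births before 34 WA lie within induced prematurity, and the objective speaks of the need for birth, so indicated delivery is the right construct. A cause-specific death endpoint is defensible for a treatment aimed at placental disease, and the wording keeps unexplained deaths in.

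Much of this stands. A reader might infer that the trial cannot answer three of its objectives. The documents do not support that: section 12.5 probably covers the first, the data for the second are a subset of a listed endpoint, and the third is answered in part. A reader might also infer that deaths from bleeding would be missed. That too is unsupported. Retroplacental haematoma is listed as a severity criterion of pre-eclampsia, so such deaths would plausibly count; cause is judged under double blinding; and death is a serious adverse event reportable whatever its cause (sections 13.1.1 and 13.1.2), although the text does not spell out that this extends to the newborn.

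What the reply does not remove is that section 12.5 names no measure, leaves the conditional line in the endpoint list and the Abstract, and is silent on the other two items. The statistical analysis plan is not at hand and may specify more, but the protocol itself fixes the mismatched wording.

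**Conclusion.** The point holds, led by the first item. As worded, the early pre-eclampsia endpoint conditions on the outcome and cannot measure prevention; that follows from its definition and needs no assumption. The size does need one: with onset assumed N(36, SD 3 to 4) and a two-week delay, early cases fall by 58% to 75% while the listed measure moves about 0.3 weeks. The normal shape is rough: the shifted curve with SD 4 puts about 16% of onsets beyond 42 WA. Only the part below 32 WA enters the calculation, and the direction of the conclusion does not depend on the exact shape.

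The missing 34 WA cut-off is a real but smaller mismatch. The restriction of perinatal death by cause is the mildest, since that endpoint answers part of its objective. No size is put on either. These are secondary endpoints: the primary endpoint, sample size and stopping rule are untouched.

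Counting occurrence asks the right question but does not make it well powered. With 2473 per arm and two-sided 5%, halving an assumed early rate of 0.5%, 1% or 2% would be detected with about 30%, 53% or 82% power.

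**What to change.** In section 7.1.1 and the Abstract, and consistently in section 12.5:

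- List occurrence of pre-eclampsia with onset before 32 WA, with all women analysed as the denominator. Keep onset age as a description of the cases only, without a between-group test.
- Replace induced prematurity by indicated birth before 34 WA; the broader category can be reported beside it.
- Report all-cause perinatal death from 22 WA to postnatal day 7 alongside the placental-cause version.
- State in section 12.5 that each is compared between arms as an occurrence.

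The cost is a few lines of text. The case report form is not shown, but onset age is needed for the endpoint already listed, gestational age at birth for the birth-weight percentile, and every perinatal death must be identified before its cause can be judged. No new data item should therefore be required, and the number of women does not change.

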# Research design

## Description of the research methodology

### Experimental plan

Randomised double-blind parallel-group trial.

The study is planned as a pragmatic trial, in the sense defined by Schwartz and Lellouch (J Chron Dis, 1967;20: 637-648), namely that the women included correspond to the primiparous population at risk (non-inclusion criteria not very restrictive), that the management methods of these women are very flexible (no modification of the usual management, except for the treatment under study) and that the endpoint is medically relevant and simple to collect.

### Description of measures taken to reduce and avoid bias

#### Randomisation

Patients will be randomised to one of the following 2 groups: the low-dose aspirin (160 mg/day) experimental group or the placebo group.

This randomisation will be stratified by investigating centre.

# On a practical level, randomisation will be configured by the Clinical Investigation Centre of the Tours University hospital and will be carried out centrally using the electronic case report form (Capture System software) implemented in this study.

#### Blinding

The study will be conducted in a double-blind manner vs placebo. Thus, neither the patient, nor the investigators, nor the healthcare team will know the nature of the treatment.

An unblinding procedure will be put in place at the level of the electronic case report form.

### Procedure under study

#### Experimental group

Patients in the experimental arm will receive low-dose aspirin (Kardegic® 160 mg/day). The choice of this dose is based on the assumption that the effect of this treatment is most likely to be greatest with the maximum dose that has proven its maternal and foetal safety.

The treatment comes in the form of sachets containing 288 g of DL-lysine acetylsalicylate powder (corresponding to an equivalent of 160 mg of aspirin) to be dissolved in water. The dosage regimen is 1 sachet/day. Treatment will be initiated at enrolment and in any case at a gestational age ≤ 15 WA completed. In the absence of intolerance or major side effects, it will be continued up to 34 WA.

#### Control group

Patients in the control arm will receive a placebo of aspirin that they will take according to the same dosage regimen as that defined for the experimental group.

### Patient follow-up

Apart from treatment (Kardegic® 160 mg/day or placebo), patients will be managed according to the usual methods of pregnancy monitoring [HAS].

## Expected duration of participation of persons and description of the timeline and duration of all test periods, including follow-up, where applicable

The duration of the study is estimated at **53** months (**47** months of inclusion and approximately 6 months of follow-up).

Note that patient follow-up is not fixed, it depends on the inclusion (between 11-15 WA) and the date of delivery.

From the first inclusion, the sponsor must inform the competent authority and the IEC, without delay, of the effective start date of the study (Effective start date = date of signature of the consent by the first patient taking part in the research)

The study end date will be sent by the sponsor to AFSSAPS and the IEC within 90 days. The research end date corresponds to the end of the participation of the last person to take part in the research, or, if applicable, **to the gestational age defined in the protocol.**

# Selection of research subjects

## Inclusion criteria

- Women ≥ 18 years of age
- Primiparous, i.e. never having had a pregnancy ≥ 22 WA.
- Having a singleton pregnancy
- At a gestational age ≤ 15 WA completed i.e. 15+6 WA
- Having a bilateral notch ≥ grade II and/or the lowest uterine artery pulsatility index value ≥ 1.7 during the first trimester ultrasound (between 45 and 84 mm CCL)
- Having given their informed consent
- Affiliates or beneficiaries of a social security scheme

## Non-inclusion criteria

- Women wishing to terminate their pregnancy (abortion, with legal gestational age ≤ 14 WA) or for whom termination of pregnancy (therapeutic abortion or premature extraction) is envisaged before the gestational age of 37 WA
- Having a foetal ultrasound abnormality detected during the first trimester ultrasound (foetal malformation or neck ≥ 95th percentile)
- On anticoagulant treatments
- With known allergy or hypersensitivity to Kardegic® or any of its components
- With primary or secondary haemostasis disease responsible for bleeding or at haemorrhagic risk
- With active gastroduodenal ulcer
- With lupus or anti-phospholipid syndrome

## Exclusion criteria

No patient will be excluded from the study, after she has been randomised (intention to treat principle). However, premature termination is possible (see §10.2.1).

## Recruitment procedures

### Selection of recruiting sonographers

The trial is conducted in collaboration with the French College of Foetal Ultrasonography (Collège Français d'Echographie Fœtale - CFEF) which has officially committed (see Appendix). The sonographers involved in patient recruitment will be selected out after validation (in the form of an Evaluation of Professional Practices - EPP). This is a pre-test PPE conducted using a procedure based on a computer tool developed by the CFEF for the quality control of foetal neck measurement [41]. Briefly: each sonographer will be asked to upload to a dedicated website, 20 digital photographs (anonymised for each patient) of Doppler ultrasound measurements of the uterine arteries during the first trimester of pregnancy (10 consecutive photographs with notching and 10 consecutive photographs without notching). Each image must include a B mode image with a colour Doppler mode window of the spectrum measurement site, Doppler window in place, along with the correctly adjusted Doppler spectrum of the uterine artery measured (gain, speed of movement, pulse repetition frequency or PRF) on which the resistance index (RI) and the pulsatility index (PI) are measured.

Each practitioner's images will then be evaluated separately, anonymously, by two experts according to a grid comprising five criteria rated 0, 1 or 2:

- Uterine artery measurement site
- Doppler scroll speed and number of cycles scanned
- PRF adjustment
- Notch assessment
- Index measurement

For an image to be considered satisfactory, it must have been rated at least 6/10.

To be validated, the practitioner must have obtained an average of 13/20, which means that at least 13 of their 20 images must have obtained a score of 6/10. A practitioner who is not validated at the time of a first evaluation may undergo a second subsequent evaluation.

This EPP will allow the practitioner to obtain the "FMC points" necessary for the validation of their regulatory Continuing Medical Training of physicians obligation.

